#### Qualitative Analyses

Each workshop and the corresponding debriefing session among PSWs will be transcribed verbatim. The data analysis team will employ thematic analysis [101-103], and a combined deductive and inductive approach to coding [104]. We are particularly interested in understanding life trajectories and transitions in relation to the five domains of the Recovery Assessment Scale and the five clusters of the Citizenship Measure. The chosen approach combines the perspective of the life course and the relational perspective of social networks. This approach makes it possible to understand the different trajectories that make up the life course of individuals in the light of the dynamic relationships that place them (or not) in support networks while taking into account their subjectivity and ability to act (agency). From the life course perspective, the development of the person is posited as a process that does not necessarily stop at predetermined stages [105]. The structured and unstructured material will also be analyzed through natural language processing [106], which is one area of artificial intelligence using computational linguistics that provides parsing and semantic interpretation of text, which allows systems to learn, analyze, and understand human language.

#### Sex and Gender

Biological sex is a categorical construct comprised of genes, anatomy, gonads, and hormones that make up male and female differences [107]. Beyond one’s birth-assigned sex, sociocultural gender refers to diverse roles, orientations, and identities that influence health across lifespan development. Sex and gender have rarely been considered together in recovery research. To address this gap, we will conduct secondary analyses stratified by sex following recent recommendations in promoting rigor and reproducibility in health research [108]. In qualitative analyses, verbatims will also be coded with considerations of participants’ sex in order to identify themes unique to men and women. For example, social support is a health-promoting factor that is experienced differently by men and women, as we have seen in a previous study with the results of the personal-civic recovery measures. In addition to sex, we will explore sociocultural gender roles using a validated questionnaire (Bem Sex Role Inventory) that will allow us to assess dimensions of masculinity, femininity, and androgyny along continuums [109,110]. Previous work by Juster et al [111] has shown how measuring gender-roles provides unique within-sex understanding of mental and physical health. In quantitative analyses, we will explore correlations among gender roles (masculine and feminine subscales) in association with study outcomes representing recovery. Taken together, our sex- and gender-based analyses will provide insights into sex-specific and gender-specific recovery.

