#### Principal Research Questions

The principal research questions are whether our novel PSWs-facilitated online intervention will have an impact in terms of (Q1) clinical recovery potential and (Q2) personal-civic recovery potential. We also question (Q3) how these potentials can be impacted by the COVID-19 pandemic and (Q4) how the lived experience of people in recovery can be mobilized to cope with the situation. Finally, we also explore (Q5) how sex and gender considerations can be taken into account for the pairing of PSWs with service users beyond considerations based solely on psychiatric diagnoses or specific MHPIs [35]. We aim to collect data for a future randomized controlled trial (RCT) [36] by clarifying a certain number of remaining uncertainties and by detecting an effect that would be specifically attributable to transitional peer support as facilitated by trained PSWs. We will thus consider scientific reasons, processes, resources, and management in preparation for a more definitive trial. Indicators of feasibility will include recruitment rates practices, participants and facilitators, as well as feasibility and retention rates in the study protocol [37].

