#### Allocation

Upon reception of the signed Information and Consent forms by email, consecutive referrals will be randomly allocated by computer algorithm to one of the two modalities at point of entry into the study on acceptation into the protocol using a computerized program (eg, randomization.com). At this entry point, the participant will have been evaluated, diagnosed, met inclusion criteria, and given formal consent for the randomization procedure. To ensure a balance in the allocation for the strata and thus control the risk of a secular trend in the composition of groups, random block sizes in a random order will be used (3, 6, 9, etc). Participants will thus be randomly allocated to the trial arm (n=20, 2 groups of 10) or control arm (n=10), and will be identified by a randomly assigned identification number. Among those allocated to the experimental groups, 10 patients with psychotic disorders will be randomly selected to be part of the transitional support group for patients with psychotic disorders, and 10 patients with anxiety or mood disorders will be randomly selected to be part of the transitional self-help group for patients with anxiety or mood disorders. It will be the same for the control group; 5 patients with psychotic disorders will be randomly selected to be part of the control group for patients with psychotic disorders, and 5 patients with anxiety or mood disorders will be randomly selected to be part of the control group for patients with anxiety or mood disorders. In both cases, those who have not been selected will be placed on a substitute list in the event of withdrawal of a selected patient, who will be replaced at random by one of the corresponding substitutes.

The groups will be studied together and separately: the experimental group for patients with psychotic disorders (n=10) will be compared to the control group for patients with psychotic disorders (n=5); the experimental group for patients with anxiety or mood disorders (n=10) will be compared to the control group for patients with anxiety or mood disorders (n=5); and the combined experimental group for patients with psychotic disorders and for patients with anxiety or mood disorders (n=20; 2×10) will be compared to the combined control group for patients with psychotic disorders and anxiety or mood disorders (n=10).

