#### Recruitment

As of February 2020, 2136 IUSMM patients have been enrolled in the Signature Bank since the year 2012, including 822 individuals with psychotic disorders, and 853 with anxiety and/or mood disorders. The study was approved by the local ethics committee in accordance with the Declaration of Helsinki, and the Signature Bank’s management framework provides further details on recruitment and consent forms. Between August 26, 2019, and February 26, 2020 (6 months), a preliminary validation study [100] allowed us to recruit 93 of the Signature Bank participants diagnosed with either psychotic disorders, or with anxiety and mood disorders. In total, 36 were female (39%) and 57 were male (61%). They further completed the Recovery Assessment Scale and Citizenship Measure, both of which a 5-point Likert scale was used to rate items. For the former, the mean was 3.77 (out of 5; SD 0.78). For the latter, the mean was 3.91 (out of 5; SD 0.63). The type of participants we need can thus easily complete our questionnaires in parallel to those of the Signature Bank. A research assistant with lived experience of an MHPI will contact by phone all the above-mentioned 93 Signature Bank participants who have already been in touch for the previous validation study and who have already accepted to be contacted again by our team for such purposes. If needed, other Signature Bank participants who meet the inclusion criteria will also be contacted until 30 Information and Consent forms are returned. The Information and Consent form will be sent by email to those who provide an email address. They will be offered CA$20 as compensation indemnity for the baseline and follow-up completions of the Recovery Assessment Scale, the Citizenship Measure, and the Bem Sex Role Inventory (see the *Sex and Gender* section).

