#### Quantitative Analyzes

Baseline characteristics will be summarized, including for the measures of clinical recovery (see the *Outcome Measures at Follow-up* section), the Recovery Assessment Scale, the Citizenship Measure (personal-civic recovery), the COVID-19 Stress Scales, and the Bem Sex Role Inventory. All participants with data at baseline (T1) and follow-up will be included in the analyses. We will compare within-patient change from baseline to intervention versus control group in the study outcome measures using the Student paired sample *t* test. The analysis will run on intervention and control practices separately so as to explore practice level impact on the differences in outcomes. Comparison of confidence interval and effect size between groups will be assessed.

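### The sex-stratified analyses are meant to speak to sex-specific recovery, but no estimate of the male-female difference is named

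*Protocol article*

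**What the plan says.** The Sex and Gender section sets the method for sex: "To address this gap, we will conduct secondary analyses stratified by sex following recent recommendations in promoting rigor and reproducibility in health research". For gender roles it plans correlations of the masculine and feminine subscale scores with the recovery outcomes. It then says what the two together are for: "our sex- and gender-based analyses will provide insights into sex-specific and gender-specific recovery".

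The Quantitative Analyzes section names one test: "We will compare within-patient change from baseline to intervention versus control group in the study outcome measures using the Student paired sample" *t* test. It goes on: "The analysis will run on intervention and control practices separately so as to explore practice level impact on the differences in outcomes". It closes with "Comparison of confidence interval and effect size between groups will be assessed", which follows the intervention and control comparison and does not mention sex.

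Under Principal Research Questions, sex and gender form the fifth question, worded as exploration: "we also explore (Q5) how sex and gender considerations can be taken into account for the pairing of PSWs with service users".

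**The concern.** To say that recovery, or the response to the intervention, is specific to one sex is to say that the sexes differ. Analyses run separately in men and in women each address a different null hypothesis: no change, or no effect, in that sex. None of the analyses named has the null of equal effects in the two sexes, and none estimates how far the effects differ.

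The strata are small and probably unequal. The same true effect can then reach significance in one sex and miss it in the other through chance and stratum size alone, and the larger stratum is favoured. An apparent benefit in men only or in women only could be carried into the question of how to pair peer support workers with service users, which is what the fifth research question explores.

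**Working it through.** The article gives no power or error-rate figure for the sex analyses, so there is none to reproduce. The check asks how often exactly one sex would be significant when the true effect is the same in both.

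**Inputs from the article**
- Allocation: "Participants will thus be randomly allocated to the trial arm (n=20, 2 groups of 10) or control arm (n=10").
- Sex mix: "In total, 36 were female (39%) and 57 were male (61"%). This is the earlier validation cohort from which the trial recruited (Recruitment section), used as a proxy. The trial's own mix is not reported.
- Applied to 20 and 10: 20 × 57/93 = 12.3 men and 20 × 36/93 = 7.7 women in the intervention arm; 10 × 57/93 = 6.1 and 10 × 36/93 = 3.9 in control. Rounded: 12 v 6 men and 8 v 4 women.
- Completers at T2 (Table 1): 7 + 10 = 17 experimental and 7 control. The analysis set is those with both baseline and follow-up data. The same mix gives about 10 v 4 men and 7 v 3 women.

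**Assumptions not in the article:** two-sided alpha 0.05; a common standardised effect d of 0, 0.3, 0.5 or 0.8. The article gives no alpha, expected effect or SD of change.

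**Formulae**
- Power within a sex uses the noncentral t distribution. Between arms: df = n1 + n2 − 2, noncentrality d / √(1/n1 + 1/n2). Paired within the intervention arm: df = n − 1, noncentrality d√n.
- P(exactly one sex significant) = pM(1 − pF) + pF(1 − pM).

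**Results**

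| Test within each sex | d | pM | pF | Exactly one |
|---|---|---|---|---|
| Any | 0 | 0.050 | 0.050 | 9.5% |
| Between arms, 12 v 6 and 8 v 4 | 0.3 | 0.087 | 0.073 | 15% |
| | 0.5 | 0.156 | 0.115 | 23.5% |
| | 0.8 | 0.325 | 0.220 | 40% |
| Between arms, completers, 10 v 4 and 7 v 3 | 0.3 | 0.075 | 0.067 | 13% |
| | 0.5 | 0.122 | 0.098 | 20% |
| | 0.8 | 0.238 | 0.176 | 33% |
| Paired, intervention arm, 12 and 8 | 0.3 | 0.158 | 0.114 | 24% |
| | 0.5 | 0.353 | 0.232 | 42% |
| | 0.8 | 0.714 | 0.496 | 50% |

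Worked line, between arms at d = 0.5: 0.156 × 0.885 + 0.115 × 0.844 = 0.138 + 0.097 = 0.235.

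The split favours the larger stratum. Paired at d = 0.8, men only occurs in 0.714 × 0.504 = 36% and women only in 0.496 × 0.286 = 14%.

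**A direct contrast on the same data.** A test of the male-female difference rejects in 5% of trials when the effects are equal. Simulation gave 4.8% to 5.2% for the arm-by-sex test. For 12/6 men and 8/4 women the standard error of the interaction, in SD units, is √(1/12 + 1/6 + 1/8 + 1/4) = 0.79 on 26 df. Its power is 9% for a true difference of 0.5 SD and 16% for 0.8 SD. The half-width of the 95% CI is about 2.056 × 0.79 = 1.6 SD, before any gain from adjusting for the T1 score.

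**The case against.** The strongest reply is that the faulty inference is not in the document. The article promises insights, names no test within strata and no alpha, and states no rule that significance in one sex alone makes an effect sex-specific. A reader might infer that rule from separate analyses and a paired test, and conclude that the plan has an error rate of up to about one half. The text does not support that, and this part of the reply stands. The rates above describe a reading that the article leaves open.

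The quantitative section also plans to compare confidence intervals and effect sizes between groups, so it does not rely on significance alone. That too is fair, although the sentence is not said to cover the sexes.

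The sex analyses are labelled secondary, and the research question is exploratory, in a feasibility study. A reader might also infer that this trial's sex results are meant to guide peer support practice. The remark about guiding practice, in the Previous Works section, concerns differences found in an earlier sample of 845 patients; for this trial that section speaks only of further exploration. Both points limit the weight of the finding.

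The last reply is that an interaction term is detail for a full protocol or SAP. This stands only in part: the article itself pairs a method with a conclusion, and stratification alone does not supply the quantity that the conclusion needs.

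Low power of the interaction test is a real limit on what the remedy can deliver. It is also the reason not to interpret significance in one sex only.

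**Conclusion.** The concern holds in a limited form. The article plans to learn about sex-specific recovery from analyses stratified by sex and names no estimate of the male-female difference.

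If one-sex significance were read as a sex-specific effect, that pattern would arise under identical effects in 9.5% of trials at d = 0, and in roughly 13% to 50% for d between 0.3 and 0.8. Where in that range depends on the test used and the number analysed. These are conditional figures, resting on the assumed effect sizes, the assumed alpha and the borrowed sex mix; none is an error rate of the plan as written. Because the analyses are secondary and exploratory, the consequence is a risk of misinterpretation and does not touch the primary comparison. It is still worth correcting, because the correction is cheap.

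**What to change.** In the Sex and Gender section, state that any sex-specific statement will rest on one exploratory model for all analysed participants, with arm, sex, the arm-by-sex interaction and the T1 score. Report the male-female difference in effect with its 95% CI. Keep the by-sex estimates with their CIs as description only. Add that significance in one sex and not in the other is not evidence of a sex difference.

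The cost is a few sentences and one extra model with data already collected. The downside is a wide interval: with about 9% to 16% power for differences of 0.5 to 0.8 SD, even with all 30 participants analysed, few sex-specific statements will be possible.

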### Ethical Considerations

Declaration of Helsinki protocols are being followed, and patients will give written informed consent. The study was approved on June 16, 2020, by the Research Ethics Committees of the Montreal Mental Health University Institute (#2020-1948). For all participants of the Signature Bank, including those participating in the research presented in this manuscript, an overseeing mental health expert have ruled that all adult patients were deemed ethically and medically capable of consenting for their participation.

## Results

This pilot study was funded in March 2020. Recruitment took place during the months of July and August 2020. Table 1 presents the distribution of recruited participants. We anticipate the publication of two key papers in accordance with the Canadian Institutes of Health Research open access policy: (1) the registered research protocol and (2) description of the main conclusions of our case-control study. Table 2 presents the calendar of activities.

**Table 1 table1:** Distributions of participants in the pilot study.

Characteristic		Participants, n (%)
**Total eligible participants (N=92)**		
	Participants with AMD^a^	31 (33.7)
	Participants with PD^b^	61 (66.3)
**Total eligible participants who agreed to receive the ICF^c^ by email (N=92)**		54 (58.7)
	Participants with AMD (n=31)	23 (74.2)
	Participants with PD (n=61)	31 (50.8)
**Total eligible participants who returned the signed ICF (n=54)**		36 (66.7)
	Participants with AMD (n=23)	17 (73.9)
	Participants with PD (n=31)	19 (61.3)
**Total eligible participants who completed the questionnaires at T1 (n=36)**		32 (88.8)
	Participants with AMD (n=17)	16 (94.1)
	Participants with PD (n=19)	19 (100.0)
**Total eligible participants who completed the questionnaires at T2 (n=30)**		24 (80.0)
	Participants with AMD in the experimental group (n=10)	7 (70.0)
	Participants with PD in the experimental group (n=10)	10 (100.0)
	Participants with AMD or PD in the control group (n=10)	7 (70.0)

^a^AMD: anxiety and mood disorders

^b^PD: psychotic disorders.

^c^ICF: Information and Consent Form.

**Table 2 table2:** Calendar of activities.

Date	Activity	
	Convergent and Concurrent Validity Between Clinical Recovery and Personal-Civic Recovery	Effects of Online and Recovery-Oriented Peer Support Groups Facilitated by Peer Support Workers
	ClinicalTrials.gov ID NCT04125030	ClinicalTrials.gov ID NCT04445324
September 2019 to March 2020	Study suspended due to the COVID-19 pandemic 92 eligible participants completed the study	—^a^
April-May 2020	—	Writing and submission of the research protocol to the institutional review board
June 2020	—	Institutional review board approval of research protocol
July 2020	Submission of the study protocol for publication in a peer-reviewed journal	Submission of the study protocol for publication in a peer-reviewed journal
August 2020	—	Recruitment of study participants among those 92 from the previous validation study Precompletion of measures (T1)
September to October 2020	Publication of the research protocol [100]	10 weekly peer support groups for patients with psychotic disorders 10 weekly peer support groups for patients with anxiety or mood disorders
November 2020	Data analyses	Postcompletion of measures (T2) Addenda to study protocol Submission of the revised study protocol for publication
December 2020	Submission of the study’s main conclusions for publication in an open access peer-reviewed journal	Data analyses Submission of the study’s main conclusions for publication in an open access peer-reviewed journal

^a^Not applicable.

## Discussion

Qualitative and quantitative results will be provided to all stakeholders and knowledge users, and posted on our massive open online course (MOOC) platform. Several PSWs and engaged service users take turns as teaching partners in *The Fundamentals of Recovery* MOOC [112], for which there are 1553 registrants from 51 different countries (Multimedia Appendix 1).

MOOCs are free interactive step-by-step courses developed by universities with the aim of reaching an unlimited number of participants and to create a community of lifelong e-learners (electronic learners). PSWs will be involved in the presentation and discussion of the findings, and acknowledged as coauthors in the publications, whenever appropriate, including within the MOOC (second edition). Indeed, the MOOC will be used as a knowledge translation platform for ongoing discussion among registrants, and updated with the findings of this pilot study in particular. Undoubtedly, the COVID-19 pandemic has disrupted many aspects of academic medical missions [113]. When the pandemic has subsided, although there will likely be some “return to normal,” some of the innovations developed in response to the COVID-19 pandemic will most likely remain a part of academic psychiatry’s everyday clinical and educational operations. The MOOC was not originally conceived as an innovative response to any particular pandemic. It has been nevertheless particularly appreciated in times of lockdown due to the COVID-19 pandemic. For the first 20 weeks of 2020, Figure 1 shows the cumulative total of registrants, whereas Figure 2 shows the weekly variations of new registrants to the MOOC; both figures show accelerated counts since WHO officials announced on March 11, 2020, that the COVID-19 contagion should henceforth be considered a pandemic.

**Figure 1 figure1:**
[figure not shown]
Cumulative total of MOOC (massive open online course) registrants during the first 20 weeks of 2020. WHO: World Health Organization.

**Figure 2 figure2:**
[figure not shown]
Weekly variations in new registrants to the MOOC (massive open online course) during the first 20 weeks of 2020. WHO: World Health Organization.

In 2017, before the current COVID-19 crisis, Bendezu-Quispe and colleagues [114] suggested that the emergence and re-emergence of communicable infectious diseases like Ebola or Zika were already increasing the necessity of knowledgeable and skilled health professionals, specifically with MOOCs arising as opportunities that allow people around the world to participate in higher-education courses. They argued that MOOCs can be used to learn about health issues of global relevance, and with the necessity of fast divulgation of knowledge and skills. Given the scope of mental health problems and the constraints of resources in training psychiatrists and other mental health professionals in most parts of the world, continuing education for medical and health or social services professionals and students, including in primary care, is vital [115]. In this MOOC, PSWs are included as training partners, as well as a subgroup of colearners.

Moreover, millions of people worldwide experienced moderate to severe levels of stress- or anxiety-related symptoms in response to COVID-19. This is true for the general population [116] as well as for people already diagnosed with psychotic disorders [117] or anxiety and mood disorders [118]. Yet, if general conditions remain the same for the participants of the experimental groups and for those of the control groups, and significantly different benefits are still observed among these groups, these differences will, in principle, be attributable to the intervention and not to the pandemic context.

Some psychiatrists even warn of a “tsunami” of mental illness due to problems arising during lockdown. They are particularly concerned that children and older adults are not receiving the support they need because of school closures, self-isolation, and fear of hospitals [119]. It could take years for some people to recover from these problems and find their own recovery pathway if they do not get support. During the pandemic, our new online intervention, combined with the MOOC, will add to already existing services. Several studies report on such experiments, such as online peer support for patients [120] but also for health professionals on the frontline of the COVID-19 outbreak [121] and whose mental health and well-being are at stake. This pandemic context indeed has major impacts on stress, anxiety, and possible depression in people who are already in treatment [122] as well as the general population and current health care workers, including PSWs. Supporting the mental health of medical staff and affiliated health care workers is a critical part of the public health response [123]. Given that three Integrated University Health and Social Services Centres affiliated with the University of Montreal—with a total of more than 40,000 employees—are supporting this pilot project, they may wish to come together and widen access to this relatively low-cost intervention for other current patients as well as their employees in need of support and information to prevent deterioration of their own mental health and recovery potential. The arrival of PSWs in the workforce as a new type of additional provider will no doubt be welcome.

Beyond the current acute context, this feasibility study of a trial and corresponding future RCT, plus the MOOC as an innovative knowledge translation strategy, have the potential to demonstrate the relevance of this online group intervention of PSWs for many more current and future patients. Indeed, the Quebec Ministerial Mental Health Action Plan currently in force mentions the Assertive Community Treatment teams as potential models for the inclusion PSWs. Several reviews concluded that Assertive Community Treatment is more effective than standard services in reducing hospital use and increasing community tenure, and numerous practice guidelines endorsed this model as an evidence-based practice for the treatment of psychotic disorders like schizophrenia [124]. Psychotic disorders affect about 1% of the population, while anxiety and mood disorders are much more common disorders from which 10% of the population experiences during normal times, a figure that will inevitably rise with the current COVID-19 pandemic and its aftermaths. There are already existing (online) self-help groups for these people, with or without PSWs, but which are not necessarily complementary to treatment offered by formal public mental health services, as is the case for people treated by Assertive Community Treatments teams where there are PSWs. Conversely, as the potential of digital mental health has become urgently apparent, the surge in interest and use of digital health to meet the demands of patients in quarantine, with social and physical distancing restrictions, and a lack of in-person care has centered on anxiety and mood disorders—and largely ignored those with psychotic disorders [120]. As uses of telehealth during the COVID-19 crisis increase, the potential of digital mental health to increase access is becoming clearer [125,126]. Access to a transitional and intermediary online self-help groups between the institutional environment and the community environment, for both people living with psychotic disorders or anxiety and mood disorders alike, could become a good practice to recommend beyond the current context of the COVID-19 pandemic.

